### Qualitative analysis

Acceptability

Qualitative feedback interviews will be anonymised and transcribed verbatim. Reflexive thematic analysis will be used to analyse the data (Braun & Clarke, 2006). Reflexive thematic analysis consists of six iterative stages including i) data familiarisation; ii) data coding; iii) initial theme development; iv) theme refinement; v) defining themes; and vi) report write-up. Reflexive thematic analysis recognises the role of the researcher (i.e., their assumptions, values experiences etc.) in shaping the data analysis (Braun & Clarke, 2006). The analysis will be led by the study researcher, who will meet regularly with other study team members to discuss codes and themes in relation to the research themes to allow for alternative interpretations of the data. Braun and Clarke's (2023) guidance on producing and reporting methodologically thematic analysis will be used to ensure quality analysis.

# Intervention

The intervention is a modular, guided self-help intervention, based on the principles of Cognitive Behavioural Therapy (CBT). This intervention (and therapist manual) has been adapted from existing guided self-help interventions for adults with eating disorders (e.g., Fairburn, 2013; Schmidt, Treasure & Alexander, 2015) and CYP with anxiety (Creswell & Willetts, 2019), to be suitable for CYP with eating disorders. These adaptations have been informed by focus groups with CYP with lived experience of an eating disorder (*n* = 11), their parents/carers (*n =* 12), and health care professionals with experience in treating eating disorders in paediatric settings (*n* = 10). These interviews and focus groups explored these key stakeholders’ views and preferences towards the content, structure and modes of delivering guided self-help interventions for CYP with eating disorders.

The intervention will consist of 8 weekly guidance sessions that will be conducted with CYP. These sessions will be 30 minutes in duration. These sessions will take place via videocall or over the telephone with the guide (study researcher). Parents/carers are encouraged to attend.

The core aims of the intervention are to provide psychoeducational material provided as part of the cognitive-behavioural treatment of eating disorders for CYP (Dalle Grave & Calugi, 2020), and to encourage CYP to change a variety of thoughts and behaviours relating to eating, body weight and body shape. Families will have access to an online website that contains all of the module content, and also interactive PDFs where they can submit their reflections. Families will be asked to work through one module from the programme each week and will also be asked to complete some activities between each session. The intervention will be piloted with families and iterative improvements will be made to the intervention following their feedback.

The intervention will be supported by the study researcher, [name], who has over 3 years’ experience of working with CYP and families with common mental health difficulties in research settings. Each support session will focus on reviewing the previous weeks’ material and activities, with the aim of facilitating adherence to the intervention. The guide’s role will be to enhance motivation, troubleshoot problems and refer the family to the programme to enhance knowledge and skills usage. The support sessions are not intended to deliver new content.

Treatment will be overseen and supervised by [name] (Clinical Psychologist), [name] (Clinical Psychologist), [name] (Child and Adolescent Psychiatrist) and [name] (Clinical Psychologist), who all have extensive experience in treating CYP with eating disorders and/or other common mental health difficulties (i.e., anxiety and depression).

**Intervention fidelity**

The intervention will be supported by [name], a postgraduate researcher with >3 years’ experience of working with children and young people with mental health difficulties in research settings. [name] will receive weekly supervision from members of her supervisory team ([name], [name], [name] and [name]) throughout the research and intervention process to ensure fidelity to the agreed protocol. Guidance sessions will be audio/video-recorded and shared with the study supervisors to be discussed weekly in clinical supervision. Procedural fidelity during the intervention phase will also be monitored through the completion of adherence to the manual checklists after each guidance session.

# Discontinuation/Withdrawal of participants from study

**Discontinuation**

As weekly symptom tracking measures are being used, the guide and their supervisors will be able to quickly detect significant deterioration. If no progress and/or deterioration is seen, and this is not attributable to other known factors (e.g., a life event), the study team will discuss possible discontinuation with the family and referral to other more appropriate sources of support. If risk is identified during the study, this will be dealt with appropriately (see section on [Risk Management](#_Risk_management_1)).

**Withdrawal**

Participants have the right to withdraw from the study at any time, without impact on their clinical care. Participants who withdraw part-way through the study will be asked (under no obligation) to complete post-treatment measures. They will be asked whether they continue to consent/assent to being contacted for the qualitative interview. Data will be analysed on an intention to treat and last measure carried forward basis. Therefore, withdrawal from the study will not result in exclusion of the data for that participant from analysis.

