Families will commence treatment up to one week after completing the baseline measures (depending on how soon they can attend their first guidance session). Families will be given access to a website and interactive PDFs, and will receive 8 individual guidance sessions via a videocall or over the telephone with a Guide. They will be asked to complete weekly questionnaires throughout the intervention to assess week-to-week changes. These weekly questionnaires will take around 15 minutes to complete each week.

CYP and their parents/carers will be asked to complete the post-treatment measures 12 weeks after completing the baseline measures. This involves reporting on the CYP’s current weight for height, completing a brief questionnaire about the CYP’s symptoms of eating disorder, anxiety and depression, and emotional and behavioural difficulties. It will also involve a questionnaire to assess the acceptability of the treatment approach. It is anticipated that these questionnaires will take approximately 30 minutes to complete.

Families will then be invited to attend a feedback appointment to review the outcomes of these post-treatment measures, and to signpost them to further support if required. This appointment is expected to be around 30 minutes in duration.

CYP, and their parents/carers, will also be invited to attend an optional qualitative interview to explore their experiences of the intervention. It is anticipated that this interview will last approximately 45 minutes.

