## Data analysis

### Quantitative analysis

Statistical analyses will be performed using IBM SPSS Statistics 27. Descriptive analyses will be used to characterise the sample, to examine the participant flow through the study and attrition rates at each stage, and to assess satisfaction with the intervention.

Baseline and post-intervention measures

Symptom change will be measured by comparing scores at baseline and end of treatment. In order to ensure that the outcomes are not affected by attrition, the analyses will be conducted using Intention to Treat methods. Paired t-tests will be used to compare differences from the baseline measures to end of treatment, and Cohen’s *d* will be used to determine effect sizes (small effect ≥ 0.2, medium effect ≥ 0.5 and large effect ≥ 0.8).

Outcomes will also be evaluated on an individual level using Jacobson and Truax (1991)’s indices of meaningful change: Reliable Change Index (RCI) and Clinically Significant Change (CSC). Achievement of RCI indicates that the observed change is unlikely to be due to measurement error, and achievement of CSC indicates that change is substantial, relative to the clinical and non-clinical ranges of scores.

Session-by-session measures

Weekly measures (ED-15-Y, GBOs, ORS/CORS and SDQ SxS) will be analysed visually.

Acceptability

The feasibility and acceptability of the guided self-help intervention will be evaluated by analysing the treatment satisfaction of participants using both questionnaire measures and qualitative interviews.

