## Risk management

If risk is identified in the screening questionnaire, the family will be contacted by a trained clinician by a research team member for further assessment. The participant will not enrol in the study and any significant risk issues will be communicated to the families’ GP and any other clinician involved in their care.

If risk is identified throughout the intervention period, the family will be contacted by a research team member for further assessment. If the risk is significant, the family will be withdrawn from the study and risk information communicated to the families’ GP and any other clinician involved in their care. Referrals or requests for referrals to other services may be made as appropriate.

A risk and safeguarding management protocol that will be followed by the research team throughout the study can be found in [Appendix 5](#Appendix5).

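### Carrying the last measure forward sets the change of a young person without 12-week data to exactly zero on the main questionnaires, so one who left because of deterioration or risk can be counted as unchanged

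*Protocol*

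**What the plan says.** The Withdrawal section of the protocol fixes the rule for missing data: "Data will be analysed on an intention to treat and last measure carried forward basis". It adds that "withdrawal from the study will not result in exclusion of the data for that participant from analysis". It also says that people who withdraw part-way will be asked, without obligation, for the post-treatment measures.

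Under Quantitative analysis the protocol says: "Symptom change will be measured by comparing scores at baseline and end of treatment". The tools are named there: "Paired t-tests will be used to compare differences from the baseline measures to end of treatment", with Cohen's d, and "Outcomes will also be evaluated on an individual level using Jacobson and Truax (1991)’s indices of meaningful change", that is, the RCI and Clinically Significant Change (CSC). The same section gives the purpose: "In order to ensure that the outcomes are not affected by attrition, the analyses will be conducted using Intention to Treat methods".

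On timing, the enrolment procedure says: "CYP and their parents/carers will be asked to complete the post-treatment measures 12 weeks after completing the baseline measures". The Measures section lists EDE-Q, PEDE-Q, CIA and RCADS as baseline and post-intervention instruments. The weekly instruments (ED-15-Y, GBOs, ORS/CORS, SDQ SxS) are different scales and are to be analysed visually. Weight is also asked for weekly, for risk and medical monitoring.

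Two rules tie leaving to outcome. Under Discontinuation, lack of progress or deterioration prompts a discussion of stopping. Under Risk management: "If the risk is significant, the family will be withdrawn from the study".

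**The concern.** A scale with only two time points has no intermediate value to carry. For a CYP without a 12-week score, last measure carried forward is baseline carried forward. Three things follow.

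- The individual result is wrong. A CYP given an imputed change of zero can never be counted as reliably deteriorated, yet the protocol's own rules make worsening CYP likely to leave.
- The group result depends on how many leave and why. It is too small if the lost did as well as completers and too large if they worsened.
- The precision is misstated. Imputed zeros are treated as observed data.

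Preliminary effectiveness is part of the primary objective, and the sample is about 10 families, so two or three imputed values carry real weight.

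**Working it through.** **No figure to reproduce.** The protocol states no power, alpha, SD or drop-out rate. The sample of about 10 follows earlier case series. The first step below follows from the measurement schedule alone; the later ones rest on assumed values.

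**Individual level.** RCI = (12-week score − baseline score) / standard error of the difference. With the 12-week score set to the baseline score, the numerator is 0 and RCI = 0, whatever the scale's reliability or the threshold used. This holds for EDE-Q, PEDE-Q, CIA and RCADS.

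**Mean change.** Let N be the number of CYP, m the number without 12-week data, C the mean improvement of completers and D the true mean improvement of the lost.

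- Truth = [(N − m)C + mD] / N
- Carry-forward = (N − m)C / N, so its error is −mD/N
- Observed-only = C, so its error is m(C − D)/N

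N = 10 is the protocol's target. Assumed: C = 1.0 EDE-Q point, SD of change 1.2, and m and D as shown.

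| m | D | Truth | Carry-forward (error) | Observed-only (error) |
|---|---|---|---|---|
| 3 | +1.0 | 1.00 | 0.70 (−0.30) | 1.00 (0) |
| 3 | 0 | 0.70 | 0.70 (0) | 1.00 (+0.30) |
| 3 | −0.5 | 0.55 | 0.70 (+0.15) | 1.00 (+0.45) |
| 4 | −1.0 | 0.20 | 0.60 (+0.40) | 1.00 (+0.80) |
| 1 | −0.5 | 0.85 | 0.90 (+0.05) | 1.00 (+0.15) |

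For example, in the third row: truth = (7 × 1.0 − 3 × 0.5)/10 = 0.55; carry-forward = 7 × 1.0/10 = 0.70.

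With C positive, observed-only is nearer the truth when D exceeds C/2, and carry-forward is nearer when D is below C/2.

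**Precision**, by simulation of the paired t-test (at least 100,000 replicates, two-sided 5%), with m = 3:

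- D = +1.0: coverage of the 95% interval under carry-forward is 87%. The chance of p < 0.05 is 65% with all 10 observed, 43% under carry-forward and 46% with the 7 completers only.
- D = −0.5: coverage is 98% under carry-forward and 87% under observed-only. The chance of p < 0.05 is 17% with all 10 observed, 43% under carry-forward and 46% under observed-only.
- D = 0: the carry-forward mean is right, but the imputed zeros shrink the average standard error from 0.40 to 0.34 and raise the chance of p < 0.05 from roughly a third to 43%.

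**The case against.** **The rule does not reach everyone.** A reader might infer that every drop-out on every scale is scored as no change. The documents do not support that. People who withdraw are asked for the post-treatment measures, and those who complete them have real scores. %Weight-for-height may be an exception, because weight is collected weekly and a later value could be carried forward; the protocol does not say whether it would be. This limit stands.

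**Observed-only analysis is not better.** This also stands. If the lost worsened, analysing completers alone overstates benefit by more than carry-forward does: an error of +0.45 against +0.15 in the third row of the table.

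**The loss of power is mostly attrition.** A reader might blame carry-forward for the fall from 65% to 43%. Completers alone reach only 46%, so carry-forward accounts for about 3 points.

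**Deterioration is not wholly hidden.** Participant flow and attrition are reported, and weekly scores are displayed, so decline before leaving can be seen there. What is lost is the RCI and CSC classification on the pre/post scales.

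**The sentence on attrition concerns intention to treat and does not name carry-forward.** True, but the Withdrawal section joins the two as one basis of analysis. Keeping everyone in the denominator does not make the outcome independent of attrition when their change is filled in.

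**This is an uncontrolled case series with no efficacy decision rule.** This lowers the severity. It does not make a wrong individual classification right.

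**Conclusion.** The point holds for CYP who give no 12-week data, on EDE-Q, PEDE-Q, CIA and RCADS. Their change and RCI are exactly zero by construction, and a CYP who left for deterioration or risk could appear as unchanged. The statement that the methods keep outcomes unaffected by attrition does not hold.

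The effect on the mean depends on assumptions that the protocol does not supply. With 3 of 10 lost, completers at +1.0 and SD 1.2, carry-forward is 30% too low if the lost resemble completers (0.70 against 1.00) and 27% too high if they worsened by 0.5 (0.15/0.55). With only 1 lost at −0.5, the error is +0.05.

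A reader might conclude that the rule flatters the intervention. That is not established, because the direction depends on how the lost fared. The protocol's withdrawal rules make the favourable direction plausible, no more.

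This should be fixed. It does not undermine the feasibility and acceptability aims.

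**What to change.** 1. In the RCI and CSC results, class CYP without 12-week data as missing, with the reason. Show those who left for risk or deterioration as such, never as unchanged.
2. Do not rest the pre/post result on carry-forward alone. Report three results side by side: observed data; baseline carried forward, labelled as such and with the number imputed; and a worst case. Conclude that there was improvement only if it holds across all three.
3. Delete or soften the Quantitative analysis sentence that says outcomes will not be affected by attrition.
4. Reconcile the Withdrawal and Risk management sections on whether families withdrawn by the team are also asked for the 12-week measures. This concerns data collection only and leaves the rules on stopping treatment as they are.

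The cost is a few lines of protocol text, slightly more analysis, and an effect statement that may be less favourable or less certain.

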# Ethical and safety considerations

The West of Scotland Research Ethics Committee 5 has granted ethical approval for this study, and ethical and safety considerations will be carefully monitored by the study research team.

**Time burden**

CYP and parents/carers will be required to complete various questionnaires and interviews throughout the study. The participant information sheets will provide clear information of what assessments will be involved and why, so that CYP and parents/carers understand the purpose of the assessments. Participants will be informed that they are free to withdraw from the study at any time they wish, without needing to provide a reason for withdrawal.

The screening questionnaire is likely to take around 15 minutes to complete. The baseline and post-intervention questionnaire measures approximately 25 minutes to complete. The baseline questionnaires up to 30 minutes to complete. The feedback appointment after the baseline questionnaires around 30 minutes. The weekly measures around 10 minutes to complete. The post-intervention acceptability questionnaire around 10 minutes to complete. The post-intervention questionnaires up to 30 minutes to complete. The post-intervention feedback appointment around 30 minutes. The optional qualitative interview around 45 minutes to complete.

Families will attend 8 x 30-minute guidance sessions with a Guide, and will also spend time reading through the intervention materials and completing the worksheets between sessions.

The inconvenience of completing questionnaires, assessments, interviews and the intervention will be minimised by offering appointment dates/times to suit the participants where possible. For example, participants will have the opportunity to complete measures electronically or over the telephone. Guidance sessions will similarly be offered over the telephone or via video call, and at a time most convenient for the family.

CYP will be provided with a £25 Amazon voucher for the additional time required to complete the questionnaires 12 weeks after completing the baseline measures. CYP, and their parents/carers, will be provided with a £25 voucher each if they decide to take part in the optional qualitative interview. CYP will therefore receive a maximum of £50 in vouchers and parents/carers a maximum of £25 in vouchers. This payment rate is in line with NIHR involve rates and reflective of the time and effort required of participants for the study.

**Potential for participant distress**

The screening questions, pre- and post-intervention measures, and weekly session-by-session measures will involve discussing thoughts and feelings that CYP, and their parents/carers, may find upsetting. These questions are similar to those used in routine clinical practice. Questionnaire measures and interviews will be conducted by a study researcher with experience in working with CYP with mental health difficulties, and their families. The researcher will be supervised by a team of clinical psychologists and a child and adolescent psychiatrist (with considerable experience working with families affected by mental health difficulties). If participants become distress during the questionnaires or interviews, participants will be reminded that they can take a break and/or withdraw from the study at any time.

Guidance sessions may also involve discussing thoughts and feelings that CYP, and their parents/carers, may find upsetting. Any distress will be managed by the study researcher with the support of the study supervisors, if necessary. CYP and/or their parents/carers (depending on who is attendance) will be reminded that they can take breaks during the guidance sessions and/or withdraw from the study at any time. It is possible that CYP, and their parents/carers, may find the treatment techniques, that they are implementing at home, upsetting. The study researcher will ensure that the treatment techniques are delivered to families in a step-by-step, gradual way to reduce the potential upset. The study researcher will have the support of the study supervisors to manage any distress.

The optional qualitative interviews may involve discussing thoughts and feelings that CYP, and their parents/carers, may find upsetting. The questions asked in the qualitative interviews will be discussed with PPI representatives and piloted before use to ensure that they are acceptable to families. The interviews will be conducted by a member of the study team with experience of working with families affected by mental health problems, who will have support from the study supervisors. CYP, and their parents/carers, will be reminded that they can take breaks during the interviews and/or withdraw from the study at any time.

The research team is made up of a number of clinically trained researchers, who will be well-placed to manage any distress should it arise, and to signpost/refer to sources of support (such as local mental health services) if necessary.

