### Screening and eligibility assessment

Once families have been recruited through one of the recruitment sites, and have completed the study consent/assent forms, their eligibility for the research will be confirmed.

Families who consent/assent to participate in the study will be asked to complete a short screening questionnaire to determine their eligibility for participation (see [Appendix 1](#Appendix1)). This will include demographic information about the CYP and their parent(s)/carer(s), confirmation of UK residency, information about prescribed psychotropic medication of the CYP, current/previous psychological support received by the CYP, brief questions to determine if the CYP is experiencing possible symptoms of eating disorders that impair their functioning and a question around current self-harm and suicidality. This questionnaire can be completed online or via telephone with the study researcher. It is expected that this questionnaire will take approximately 15 minutes to complete. If families are not eligible for the study, the study researcher will contact the family to explain why they are not eligible for the research, and signpost them to relevant support, as necessary. If the screening questionnaire indicates that the family meet the eligibility criteria, they will be invited to enrol in the study.

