### Procedure once participants are enrolled

Once participants are enrolled into the study, CYP and their parents/carers will be invited to complete the baseline measures, including a battery of questionnaires, including the self-report of the Eating Disorder Examination Questionnaire [EDE-Q] and the parent-report of Eating Disorder Examination Questionnaire [PEDE-Q]). This is to confirm that the intervention is appropriate (i.e., that the CYP has impairing symptoms of eating disorders and an absence of significant risk as detailed in the inclusion/exclusion criteria). Families may also be asked to complete the online Development and Wellbeing Assessment (DAWBA) to enable an understanding of comorbid diagnoses. Note – the DAWBA will be piloted with families in the first instance. If the family have already completed the DAWBA during their assessment with the eating disorder service, this data will be accessed to prevent duplication of measures. Following the pilot, it may be decided to no longer use the DAWBA, and families will be asked to complete the Strengths and Difficulties Questionnaire (SDQ) at baseline instead.

Questionnaires will be sent to families to complete online (or over the telephone if preferred). The questionnaires will cover some additional demographic information about the family ([Appendix 2](#Appendix2)), brief questions about the CYP’s eating disorder symptoms and how they impair their functioning, and symptoms of anxiety and depression. They will also be asked to report on the CYP’s current weight and height. It is expected that these questionnaires will take approximately 15 minutes to complete. Families may also complete the DAWBA online (or over the telephone with a researcher if preferred) which will take around 45 minutes to complete.

Families will then be invited to attend a feedback appointment where the study researcher will feed back the information obtained from the questionnaires, and to discuss next steps regarding the intervention. This feedback appointment is likely to last around 30 minutes. The family will be given a report summarising the outcomes of the questionnaires and the next steps for treatment. The family’s GP and other teams involved in their care (e.g., eating disorder service) will also be sent a copy of this report to inform them about the family’s participation in the study.

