### Optional qualitative interview

All CYP, and their parents/carers, who start the treatment will be invited to attend separate optional qualitative interviews to explore their experience of receiving the intervention and acceptability of the treatment approach. Families who dropout of the study, and explicitly state that they do not wish to be contacted, will not be invited to take part.

Interviews will cover what families found helpful/unhelpful about the intervention, views on the mode, content and structure of the treatment and suggestions for improvement. An indicative topic guide can be found in [Appendix 4](#Appendix4). Qualitative interviews will be conducted over videocall or via the telephone by a member of the research team who did not deliver the treatment (e.g., an Honorary Research Assistant).

*Treatment completion/drop-out rates*

Information regarding rates of recruitment, retention, completion of measures and proportion of sessions attended by the participants will be recorded to examine feasibility.

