# Data recording and record keeping

Measures will be completed online via a REDCap form, and anonymous data inputted into a statistical programme. Computerised data will be kept on an anonymous password-protected database. The participants will be identified by a unique participant ID in any database. The name and any other identifying detail will not be included in any study data electronic file.

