**Appendix 3. Treatment acceptability questionnaire (adapted from Creswell et al., 2010)**

|  |  | Strongly disagree | Disagree | Neither agree or disagree | Agree | Strongly agree |
| --- | --- | --- | --- | --- | --- | --- |
| 1. | Overall, I am satisfied with the treatment I received |  |  |  |  |  |
| 2. | I am satisfied with the programme I received |  |  |  |  |  |
| 3. | I am satisfied with the support I received from the guide |  |  |  |  |  |
| 4. | I am satisfied with the number of support sessions I received |  |  |  |  |  |
| 5. | I am satisfied with the length of the support sessions I received |  |  |  |  |  |
| 6. | I am satisfied with the outcomes of the treatment I received |  |  |  |  |  |
| 7. | I would recommend this treatment approach to other families |  |  |  |  |  |

| 8. What aspects of this treatment did you like the most? |
| --- |
|  |

| 9. What aspects of this treatment did you like the least? |
| --- |
|  |

| 10. How can we improve this treatment for families in the future? |
| --- |
|  |

| 11. Please provide any other feedback or comments |
| --- |
|  |

*Adapted from: Creswell, C., Hentges, F., Parkinson, M., Sheffield, P., Willetts, L., & Cooper, P. (2010). Feasibility of guided cognitive behaviour therapy (CBT) self‐help for childhood anxiety disorders in primary care. Mental Health in Family Medicine, 7(1), 49–57.*

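### The protocol does not stop the guide from taking the 12-week and acceptability questionnaires by telephone, although it requires a non-delivering interviewer for the qualitative interview

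*Protocol*

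**What the plan says.** On delivery, the Protocol's Intervention section states: "These sessions will take place via videocall or over the telephone with the guide (study researcher"). Intervention fidelity describes this person as a single postgraduate researcher under weekly supervision.

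On collection of the measures, Potential for participant distress states: "Questionnaire measures and interviews will be conducted by a study researcher with experience in working with CYP with mental health difficulties". Procedure once participants are enrolled gives the mode: "Questionnaires will be sent to families to complete online (or over the telephone if preferred"). Time burden repeats the choice: "participants will have the opportunity to complete measures electronically or over the telephone". Data recording and record keeping mentions only the online route: "Measures will be completed online via a REDCap form, and anonymous data inputted into a statistical programme". Appendix 5 counts telephone and video contacts for questionnaires among the study researchers' activities (section 2) and gives them their own risk procedure (section 4.2).

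The acceptability questionnaire in Appendix 3 is part of the 12-week assessment. Its third item reads: "I am satisfied with the support I received from the guide".

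For the qualitative interview only, the protocol separates delivery from data collection. It is to be done "by a member of the research team who did not deliver the treatment (e.g., an Honorary Research Assistant").

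**The concern.** Acceptability and preliminary effectiveness are both in the primary objective. The study is a single-group case series of about 10 families. Symptom change is tested by paired t-tests from baseline to end of treatment, and acceptability is judged from the questionnaire together with the interviews. The symptom and impairment scales are self- or parent-reported, so they depend on candour.

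Someone who answers by telephone to the person who has guided them may soften criticism or report fewer symptoms. For satisfaction, measured once, any such tendency goes straight into the score. For symptom change, only the part that differs between baseline and 12 weeks matters. Reluctance to disappoint the guide would arise mainly at 12 weeks, because at baseline no guidance session has taken place. There is no comparison arm in which it could cancel, and if the mode of completion is not recorded, no later analysis can separate it out.

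The protocol accepts this reasoning for one of its two sources of acceptability data and leaves the other open.

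**Working it through.** The protocol gives no figure on this point, so there is nothing to reproduce. The check is a comparison of the text, followed by an illustration that rests on assumed inputs.

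**1. Can the guide be the person who takes the answers?**

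- Delivery: the guide is the study researcher (Intervention; Intervention fidelity).
- Collection: a study researcher, with no exclusion of the guide (Potential for participant distress). The supervision described there, by clinical psychologists and a child and adolescent psychiatrist, matches the guide's own.
- Named telephone administrator: the study researcher is named only for screening, "This questionnaire can be completed online or via telephone with the study researcher". For the baseline DAWBA it is an unspecified researcher. For the 12-week measures no one is named.
- Appendix 5 speaks of study researchers in the plural.

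So the guide as caller at 12 weeks is permitted by the text but not stated.

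**2. Which data are exposed?** Only questionnaires completed by telephone, with the guide as caller. Online forms are outside the concern, and so are the qualitative interviews, which have their own safeguard.

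**3. How large could it be?** Let f be the share of participants who answer the guide by telephone at 12 weeks, and b the resulting shift in their answers relative to baseline. The mean then moves by f × b. Neither f nor b is in the documents.

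In scale points, assuming 3 of 10 use the telephone:
- a 1-point rise on a 5-point satisfaction item moves the mean by 0.3 × 1 = 0.3;
- a 0.5-point lower EDE-Q moves the mean change by 0.3 × 0.5 = 0.15.

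If all 10 did so, the figures would be 1.0 and 0.5.

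In terms of the paired t-test, assume n = 10, a two-sided 5% level (the protocol states none), no true change, and b in standard deviations of the change score. Significance needs an observed standardised change of t(0.975; 9)/√10 = 2.262/3.162 = 0.715. The chance of a significant apparent improvement is 1 − F(2.262), where F is the noncentral t distribution with 9 degrees of freedom and noncentrality f × b × √10:

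| f | b = 0.2 | b = 0.3 | b = 0.5 |
| --- | --- | --- | --- |
| 0 | 2.5% | 2.5% | 2.5% |
| 0.25 | 3.5% | 4.0% | 5.4% |
| 0.5 | 4.7% | 6.3% | 10.6% |
| 1 | 8.2% | 13.4% | 29.3% |

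This treats the shift as a move in the mean only. The extra variance from mixing shifted and unshifted participants is b² × f × (1 − f), at most 0.5² × 0.25 = 0.0625 against a variance of 1, and is ignored. The table shows how the result depends on f and b; it does not estimate the bias in this study.

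**The case against.** A reader might infer that the guide does administer the outcome and acceptability questionnaires, and that improvement and satisfaction are therefore biased upward. The documents do not support that. Online self-completion is the default, and the telephone is the family's option. The sentence on who conducts the measures comes from a section on managing distress and says a study researcher, not the guide. The only questionnaire for which the study researcher is named as telephone administrator is screening, before any guidance session. The team also includes others who could make the calls.

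Further points stand. A family that uses the telephone at both time points carries any constant under-reporting in both scores, and it cancels in the change. No outcome is rated by an interviewer. Acceptability does not rest on the questionnaire alone: the independent interview also asks about the support sessions, including rapport. The magnitudes above are assumptions multiplied together, and the rows with high telephone use sit poorly with an online default.

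These arguments reduce the concern to a risk in a subset of families. They do not remove it. The text leaves open who calls at 12 weeks, an item about the guide is among the questions, and the protocol's own safeguard stops at the interview. A constant tendency would cancel in the change score, but one that comes from eight sessions with the guide would not, and nothing cancels in the satisfaction score.

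**Conclusion.** The point holds as a gap in the protocol. The guide is not prevented from taking the 12-week outcome and acceptability questionnaires by telephone, including the item about the guide, while the qualitative interview is protected. The consequence is a risk of inflated satisfaction and pre-post improvement among families who choose the telephone and are called by the guide. It is zero if all complete online or are called by someone else, and otherwise grows in proportion to telephone use. Its size cannot be derived from the documents, and its upward direction is plausible rather than shown.

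It is worth correcting before data collection. Who collects an outcome is a protocol procedure, and analysis cannot repair the problem afterwards.

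**What to change.** In the 12-week paragraph of Procedure once participants are enrolled, and in Potential for participant distress, state that when a family chooses the telephone for the 12-week or acceptability questionnaires, the call is made by a team member who did not deliver the sessions, as already required for the qualitative interview. Record the mode of completion at baseline and at 12 weeks, so that it can be reported with the results.

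The same edit can align the distress section, which says a researcher conducts the measures, with the sections that describe online completion.

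The cost is protocol wording and some scheduling of short calls by an existing team member for the families who prefer the telephone. No new post is needed.
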